#### Statistical Analysis

Aim 1 of phase 1: *t* tests will be used to determine if time to stabilization during the P&R differs between healthy subjects and subjects <48 h after concussion. Linear regression models will assess group differences while controlling for potential confounders of age, sex, contact/noncontact sport, and BMI. Concussion history will be recorded and explored as a covariate if necessary. As clinical scores are ordered with three levels, Wilcoxon Mann-Whitney *U* tests and generalized linear models for ordered multinomial outcomes (ordinal logistic regression) will compare clinical scores between groups. If the clinical scores exhibit a high ceiling effect, scores will be dichotomized and analyzed using χ^2^ tests and logistic models. *t* tests will assess whether concussed athletes had greater differences between single- and dual-task conditions relative to controls.

Aim 2 of phase 1: Bonferroni-adjusted *t* tests will be used to compare groups PostRTP to determine whether athletes with a recent mTBI take longer to stabilize during reactive postural responses after being medically cleared to RTP. Analogous secondary tests will be used for the PreRTP and 6Month assessments. We will also compute the difference in time to stabilization between assessments (e.g., change from Acute to PostRTP) to determine whether concussed athletes improved their postural responses over time. *t* tests will compare the group differences in the change between assessments. Longitudinal analysis using generalized estimating equations (GEEs) with compound symmetry working covariance models will be used to contrast each outcome of the P&R test at each assessment while controlling for lean direction; single vs. dual task; and possible confounders of age, sex, contact/noncontact sport, and BMI. A group-by-assessment interaction will determine if adjusted group differences changed between assessments. Two- and three-way interactions with task (group × task, group × task × assessment) will be included to test for group-difference in task, and if significant, final models will include these interactions. Ordinal logistic regression in a GEE framework will be used to assess changes in clinical scores between assessments.

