
Numerous research groups suspect that there is a link between impaired neuromuscular control and musculoskeletal injuries after mTBI. Notably, both of these aspects have solid grounding in the literature; deficits in neuromuscular control after mTBI are widely reported in the literature (Howell et al., 2018b; Wilkerson et al., 2018) and musculoskeletal injuries are around two times more likely after mTBI (Nordström et al., 2014; Lynall et al., 2015, 2017; Pietrosimone et al., 2015; Brooks et al., 2016; Cross et al., 2016; Gilbert et al., 2016; Herman et al., 2017; Fino et al., 2019; Reneker et al., 2019). Recently, dual-task gait impairment after mTBI has been linked to musculoskeletal injury risk (Howell et al., 2018a). Despite the overlap and apparent connection, a concrete connection between post-mTBI deficits and musculoskeletal injuries has yet to be established. Although absent from mTBI literature to date, imprecise responses following a loss of balance may contribute to the high rate of musculoskeletal injuries after mTBI. In healthy collegiate athletes, postural responses following the release of a sustained force at the trunk, with the lower body fixed, are highly associated with future injuries to the low back (Cholewicki et al., 2005) and knee (Zazulak et al., 2007). Disrupted perception–action coupling has been suggested as an alternative potential mechanism for post-mTBI musculoskeletal injury. This theory suggests that neurophysiological dysfunction stemming from mTBI dysregulates the perception–action coupling loop (Eagle et al., 2020); misestimating one's abilities (both the participant's physical abilities related to the environment and the participant's perception based on repeated action in the environment) may manifest in improper timing of movement or body position and increase behavioral risk after mTBI (Eagle et al., 2020). However, direct experimental evidence is lacking.

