#### Inclusion and Exclusion Criteria

For phase 1, inclusion criteria for mTBI recruitment are (1) age 18 to 30 years, (2) current participant in NCAA Division I athletics, and (3) mTBI within last 10 days (subjects must be assessed before beginning RTP protocol, even if acute time point is missed). Exclusion criteria for mTBI subjects are (1) previous history of vestibular or somatosensory pathology, (2) history of major injury to either leg requiring surgery within the last 2 years, and (3) body mass index (BMI) >40 kg/m^2^. Inclusion criteria for matched controls are (1) age 18–30 years, (2) current participant in NCAA Division I athletics. Exclusion criteria for healthy control subjects are (1) previous history of vestibular or somatosensory pathology, (2) recent mTBI (<1 year), (3) history of major injury to either leg requiring surgery within the last 2 years, and (4) BMI >40 kg/m^2^.

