Questions adapted from the OSU TBI-ID	Concussion history	Both	Acute, 6 month
Questions regarding recent (<2 years) lower extremity musculoskeletal injury and surgery history	Lower extremity injury and surgery history	Both	All
Questions regarding return-to-learn progress	Return-to-learn	mTBI	All
Questions regarding medication use postconcussion	Medication use	mTBI	All
**Test**	**Purpose**	**Subject group**	**Time point**
Clinical reaction time (drop stick test)	Clinical reaction time	Both	All
Instrumented balance error scoring system	Static balance	Both	All
Push and release test	Reactive postural response	Both	All

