#### Statistical Analysis

Time from first team activity to first musculoskeletal injury will be summarized using Kaplan–Meier methods. Cox proportional hazards models will be constructed to determine if time to stabilization during postural responses is associated with faster times to injury in the general collegiate athlete population (hypothesis 3a). Similar models will be performed for each secondary outcome. Models will first be unadjusted and then potentially adjusted for age, gender, sport, history of a recent musculoskeletal injury, and history of mTBI before enrollment. The number of variables that we will adjust for will depend on the number of musculoskeletal injuries observed. The inclusion of sport as a covariate will account for variation in the biomechanical demands, exposures, and schedules across different sports. To determine if time to stabilization is a better predictor of future injury than clinical score, similar models will be constructed for the P&R clinical score, and we will assess each model's predictive ability using c-statistics (hypothesis 3b). Models with the highest c-statistic value will indicate the outcome most predictive of time to injury.

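### Phase 1 records recent leg injury in both groups at every visit but leaves it out of its stated confounder lists, so a non-surgical leg injury could add modestly to a group difference read as an mTBI deficit

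*Protocol article*

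**What the plan says.** All references are to the protocol article.

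- **Phase 1, Statistical Analysis, Aim 1.** After the t tests, "Linear regression models will assess group differences while controlling for potential confounders of age, sex, contact/noncontact sport, and BMI". One further covariate is mentioned: "Concussion history will be recorded and explored as a covariate if necessary".
- **Phase 1, Statistical Analysis, Aim 2.** The lead analysis is unadjusted: "Bonferroni-adjusted *t* tests will be used to compare groups PostRTP". The longitudinal GEE controls for lean direction, task and "possible confounders of age, sex, contact/noncontact sport, and BMI".
- **Phase 1, Assessment Procedures, Table 1.** One row reads "Questions regarding recent (<2 years) lower extremity musculoskeletal injury and surgery history", for both groups and all time points.
- **Phase 1, Inclusion and Exclusion Criteria.** The only leg-related exclusion, the same in both groups, is "history of major injury to either leg requiring surgery within the last 2 years".
- **Introduction.** "musculoskeletal injuries are around two times more likely after mTBI".
- **Phase 2, Statistical Analysis.** The Cox models may be adjusted for, among other variables, "history of a recent musculoskeletal injury".

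**The concern.** The primary phase 1 outcome is time to stabilization after a forced step, and step latency and step length are secondary. A sprained ankle or strained thigh can plausibly change all three. The groups are not randomised, so the covariate lists have to deal with differences between them, and these lists omit a relevant variable that is already collected.

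The groups could differ in leg injury for three reasons:

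- **Before entry.** Controls with an mTBI in the past year are excluded, but cases with an earlier mTBI in that year are not. If injury is more frequent after mTBI, as the Introduction says, cases may enter with more recent injury.
- **In the mTBI event.** Nothing excludes a non-surgical leg injury from the same collision.
- **After enrolment.** The protocol expects more injuries after mTBI, and the last visit is about six months later.

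Each would push toward hypothesis 2, which expects deficits against controls at every time point. At stake is how firmly a group difference can be attributed to the mTBI itself.

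**Working it through.** **Planned figure.** The Sample Size section gives 74% power at PostRTP for d = 0.72, two-sided alpha 0.0125 and 40 per group. A noncentral t calculation (df = 78, noncentrality 0.72 × √(40/2) = 3.22) gives 74.5%, so the figure reproduces. The omission changes no stated number; 0.72 serves below only as a yardstick.

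**Inputs from the article.**
- Annual injury rate 22% (Phase 2, Sample Size Justification)
- About a twofold risk after mTBI (Introduction)
- Last visit at about 6 months (Phase 1, Assessment Procedures)
- 40 per group

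**Assumptions.**
- 22% is the control rate, with a constant hazard, doubled after mTBI.
- Everyone injured since the index date still shows the effect on the test day.
- An injury lengthens time to stabilization by δ = 0.5 to 1.0 SD, with 1.5 SD as an upper case. The documents give no value for δ.

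**New injuries by 6Month.**
- Controls: 1 − 0.78^0.5 = 11.7%
- Cases: 1 − 0.78^(2 × 0.5) = 22.0%
- Gap: 10.3 percentage points

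The contributed difference is gap × δ. For the false-positive rate it is divided by √v, where v = 1 + ½[p₀(1 − p₀) + p₁(1 − p₁)]δ², and the same t test is applied. For δ = 1.0: v = 1 + ½(0.103 + 0.172) = 1.137, standardised difference 0.103/1.067 = 0.097, noncentrality 0.097 × √20 = 0.43.

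| δ (SD) | Difference (SD) | Share of 0.72 | Rate at nominal 1.25% | Rate at nominal 5% |
|---|---|---|---|---|
| 0.5 | 0.05 | 7% | 1.5% | 5.6% |
| 1.0 | 0.10 | 14% | 2.1% | 7.1% |
| 1.5 | 0.15 | 21% | 2.9% | 9.2% |

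**New injuries by PostRTP**, if clearance comes at one month (assumed): 2.0% against 4.0%. The gap of 2.0 points gives 0.01 to 0.02 SD for δ = 0.5 to 1.0, and 0.03 SD for δ = 1.5. The nominal 1.25% becomes at most 1.32%.

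**Injury at entry or in the mTBI event.** The documents give no frequency, so no estimate is possible. As a conversion only, each 10-point excess in cases still affected at a visit would contribute 0.10 × (0.5 to 1.0) = 0.05 to 0.10 SD there.

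**The case against.** The case against is substantial, and most of it limits the size of the point.

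- **The rates are not leg-injury rates.** A reader might infer that the protocol calls leg injury twice as likely after mTBI. The Introduction says this of musculoskeletal injuries in general. The 22% is likewise for musculoskeletal injuries, and phase 2's injuries of interest include pelvis, lumbar spine and abdomen. This stands.
- **The 6Month figures lean high.** They assume no recovery before testing and give cases full playing exposure although they are held out until cleared. This stands.
- **The groups are partly aligned.** Controls are teammates matched on position and practice exposure. Progress to return to play requires a normalised BESS, which includes single-leg and tandem stance and so partly screens for a disabling leg injury. This makes a large PostRTP imbalance less likely but does not rule one out.
- **Phase 2 does not contradict phase 1.** A reader might take its use of injury history as an admission that it confounds postural response. There, injury is the outcome and the adjustment is only potential, so no inconsistency follows.
- **Later injury is downstream of mTBI.** On the protocol's own hypothesis, mTBI impairs the response and the impaired response leads to injury. Dropping visits after a new injury may remove the athletes with the worst balance and pull the estimate toward no difference. This stands, and it rules out making the persistent-deficit conclusion depend on such an analysis.
- **The detail may sit in an unseen analysis plan.** This carries less weight. The article states its confounder lists, once for each aim, and leaves out a variable it collects at every visit.
- **The lead tests are unadjusted t tests.** An added covariate does not alter them. It strengthens the adjusted analyses that support them.

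**Conclusion.** The point holds in limited form. The phase 1 confounder lists omit recent lower extremity injury, although it is recorded in both groups at every visit and could affect the outcome directly. A non-surgical leg injury present at entry or sustained in the mTBI event could contribute to a difference read as an mTBI deficit.

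The quantified part is about 0.05 to 0.10 SD at 6Month, a secondary visit. It rests on the general musculoskeletal rates and an assumed injury effect of 0.5 to 1.0 SD. New injuries matter little at PostRTP if clearance comes within about a month. The part due to injury at entry or in the same event cannot be sized from the documents.

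A reader might infer that leg injury could account for the whole of a persistent deficit. The figures do not support that: even at 1.5 SD, new injuries contribute 0.15 SD against a planning effect of 0.72. The reason to act is that the data are in hand and the improvement is nearly free.

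**What to change.** 1. Add lower extremity injury in the 2 years before the index mTBI (yes/no) to the covariates of the phase 1 linear regression and GEE models. For controls, use the 2 years before the matched case's index date. Take it from the questionnaire at the first visit attended. This variable precedes the exposure, so adjusting for it does not remove any effect of the mTBI.
2. As a supportive sensitivity analysis only, repeat the group comparisons without assessments made while the athlete reports a leg injury sustained at or after the index date.
3. Tabulate leg injury status by group and visit.
4. State in the plan that later injury may be a consequence of impaired balance, so the analysis in item 2 may be biased toward no difference. The primary conclusion should not depend on it.

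**Cost.** One extra model term and some loss of visits in the sensitivity analysis, with no new participants or visits. Separating injury before the index date from injury at or after it needs the injury date. The article states that the date is recorded in phase 2 but does not say so for phase 1. If the phase 1 questions do not ask for it, one field has to be added.

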Similar to static balance and gait, clinical assessments of reactive postural responses in other populations rely on scoring guidelines based on visual observation, but wireless, wearable inertial sensors can improve the accuracy of these assessments. For example, inertial sensors can detect differences in reactive postural responses between disease states [healthy control, multiple sclerosis (Smith et al., 2016; El-Gohary et al., 2017), Parkinson disease (Smith et al., 2016)]. Wearable sensors also provide information about quality of movement using a variety of objective characteristics. However, no study has used inertial sensors to quantify reactive postural responses in clinical mTBI settings. Improved understanding of how mTBI impacts the quality of balance recovery is critical to determine the implications of persistent balance impairments after mTBI, such as increased injury risk, and to develop clinical rehabilitation strategies to optimize athletes' neuromuscular control prior to return to competitive activity.

Our central hypothesis is that the high rate of musculoskeletal injuries after mTBI is in part due to impaired postural responses and balance recovery. Therefore, the purpose of this study is to (1) characterize reactive postural responses in athletes with recent mTBI compared to healthy control subjects, (2) determine the extent to which postural responses remain impaired in athletes with recent mTBI who have been cleared to RTP, and (3) determine the relationship between postural responses and acute lower extremity musculoskeletal injuries in a general sample of healthy collegiate athletes. We hypothesize that (1a) athletes with recent mTBI will take longer to regain balance during assessments of reactive postural responses compared to control athletes; (1b) athletes with recent mTBI will have larger deficits, in postural responses when simultaneously performing a dual task, relative to single task; (2) athletes with recent mTBI will improve reactive postural responses but will still demonstrate deficits compared to control subjects at all time points; (3a) that impaired postural responses at a baseline assessment will be associated with a faster time to acute musculoskeletal injury in healthy collegiate athletes; and (3b) objective measures of reactive postural responses will be better predictors of musculoskeletal injuries compared to clinical measures.

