### Phase 1: Characterization of Postural Responses After mTBI and Persistent mTBI-Related Deficits

#### Participants

For phase 1, 80 subjects will be recruited (40 athletes who experienced recent mTBI and 40 healthy teammate controls, matched on position and practice exposure). Sports medicine fellowship–trained team physicians with at least 10 years of training and clinical experience will diagnose mTBI based on history and physical examination, which is currently the gold standard. All subjects will be between the ages of 18 and 30 years and tested on site in the Athletic Training Clinics at the University of Utah. Informed written consent will be obtained from all participants.

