#### Sample Size

The sample size for aim 1 of phase 1 was calculated from differences between symptomatic concussed subjects and healthy controls in response to a tethered pull perturbation (Pan et al., 2015), with an estimated difference of 1.7 standard deviations (Cohen *d* = 1.7) between concussed subjects with residual balance complaints and healthy controls. With an effect size of 1.7, we will have >99% power to detect group differences at acute assessments with a 0.05 significance level and a two-sided *t* test with 40 subjects per group.

The sample size for aim 2 of phase 1 was based on an estimated effect size of Cohen *d* = 0.72 between asymptomatic, previously concussed individuals and healthy controls (Pan et al., 2015). If we observe a similar effect size of 0.72 for the P&R test, we expect 74% power to detect group differences at the primary PostRTP time point using a two-sided *t* test at a Bonferroni-corrected significance level of 0.0125 (0.05/4 for four outcomes: time to stabilization, step latency, step length and clinical score) with 40 subjects per group. Comparisons at PreRTP and 6Month assessments will also be performed but will be considered secondary. We also expect 88% power to detect group differences in the change between acute and subsequent assessments with 40 subjects per group.

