
The ability to carry out multiple tasks simultaneously, or to divide attention, is important in maintaining postural stability. Dual-task paradigms challenge the capacity for divided attention by requiring the participant to deal with competing cognitive and motor demands (Yogev-Seligmann et al., 2008). Because attentional capacity is limited, simultaneous performance of the tasks will cause a decline in one or both of the tasks (Posner and Boies, 1971; Kahneman, 1973). Correspondingly, dual-task deficits after mTBI during standing balance (Cavanaugh et al., 2005) and gait (Howell et al., 2013a, 2017) persist longer than motor tasks alone. If we find that reactive postural responses are impaired only in athletes with recent mTBI when performing a simultaneous cognitive task, it suggests that clinical evaluations of reactive balance control after mTBI should incorporate complex cognitive environments similar to gameplay. This finding would add support to existing literature demonstrating the need for dual-task assessments involving both physical and cognitive demands similar to those experienced during athletic competition.

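### The final Aim 2 GEE keeps the group × task interactions only if they are significant, which distorts the adjusted task-specific deficits (minor)

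*Protocol article*

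**What the plan says.** The Phase 1 Statistical Analysis section (Aim 2) plans a GEE for each Push and Release outcome across the assessments. It adjusts for lean direction, task and possible confounders, and it has a group-by-assessment interaction. The two- and three-way interactions with task "will be included to test for group-difference in task, and if significant, final models will include these interactions".

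Task matters elsewhere in the article:

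- Hypothesis 1b in the Introduction is that athletes with recent mTBI "will have larger deficits, in postural responses when simultaneously performing a dual task, relative to single task".
- The section on the Push and Release paradigm justifies the dual-task condition by its greater sensitivity after the acute phase.
- The Discussion cites dual-task deficits in standing and gait that last longer than single-task ones. It continues: "If we find that reactive postural responses are impaired only in athletes with recent mTBI when performing a simultaneous cognitive task, it suggests" that clinical evaluation should include demanding cognitive conditions.

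Under Aim 1, the same Statistical Analysis section also plans t tests of whether the single-to-dual difference is larger in concussed athletes than in controls. Those tests carry no condition.

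The Sample Size section gives power for group differences and for group differences in change. It gives none for an interaction with task.

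**The concern.** Choosing the final model by a significance test on the term of interest is pretest selection. If both interactions are dropped, the reduced GEE still has task as a main effect but forces the same mTBI-control difference on single and dual task at each visit. If only the two-way term survives, the dual-task excess is forced to be the same at every visit.

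If a real interaction is missed, the single-task deficit is overstated and the dual-task deficit understated, and the intervals ignore the selection step. If the interaction is kept, its estimate is inflated, because only large estimates pass the test. What is at stake is the adjusted answer to whether a dual-task deficit remains at PreRTP, PostRTP and 6Month when a single-task deficit is smaller or gone.

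**Working it through.** **The plan's own figures.** Inputs from Participants and Sample Size: "80 subjects will be recruited (40 athletes who experienced recent mTBI and 40 healthy teammate controls"; d = 0.72; two-sided α = 0.0125. The two-sample t test has 78 degrees of freedom and noncentrality d·√(n/2) = 0.72 × √20 = 3.22. Power is 74.5%, which reproduces "If we observe a similar effect size of 0.72 for the P&R test, we expect 74% power to detect group differences". The same d at α = 0.05 gives 88.9%, which fits "We also expect 88% power to detect group differences in the change between acute and subsequent assessments with 40 subjects per group". Both figures concern group differences, not the interaction.

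**Power for group × task at one visit.** This is a two-sample t test on each athlete's dual-minus-single difference. The article gives neither the size of the interaction nor the correlation r between tasks, so both are assumed. With outcome SD 1, the difference has SD √(2(1 − r)). Assume deficits of 0.3 SD (single) and 0.6 SD (dual), so the true interaction is 0.30, with α = 0.05:

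| r | SD of difference | standardised interaction | power = share of trials in which it is kept |
|---|---|---|---|
| 0.5 | 1.00 | 0.30 | 26% |
| 0.7 | 0.77 | 0.39 | 40% |
| 0.8 | 0.63 | 0.47 | 55% |

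**Simulating the rule** (20,000 trials per row, one visit). If the interaction is significant, the task-specific difference and its interval are used. Otherwise the common difference is used for both tasks.

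| r | bias, single / dual (SD) | coverage of nominal 95% intervals | mean interaction when kept (true 0.30) |
|---|---|---|---|
| 0.5 | +0.07 / −0.08 | 89% | 0.57 |
| 0.7 | +0.06 / −0.06 | 91% | 0.46 |
| 0.8 | +0.04 / −0.04 | 92–93% | 0.40 |

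Always keeping the term gives 95% coverage in every row.

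**Hand check of the bias.** The reported dual-task difference equals the task average, plus half the estimated interaction when that is kept. Its expectation is therefore 0.45 + 0.5 × P(kept) × mean kept interaction.

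- r = 0.5: 0.45 + 0.5 × 0.263 × 0.573 = 0.525, against a true 0.60 (bias −0.075).
- r = 0.8: 0.45 + 0.5 × 0.550 × 0.398 = 0.559 (bias −0.041).

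**Precision.** The standard error of a task-specific difference is √(2/40) = 0.224. That of the task-averaged difference is √((1 + r)/2 × 2/40) = 0.194, 0.206 and 0.212 for r = 0.5, 0.7 and 0.8. The narrower interval after dropping the term is one reason why coverage falls.

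**Effect of pooling visits.** If the excess is constant over four visits and the visit-to-visit correlation c of the dual-minus-single difference is 0.3 to 0.7 (assumed), its variance is multiplied by (1 + 3c)/4. Power for the same interaction becomes 32–49%, 49–70% and 66–86% for r = 0.5, 0.7 and 0.8.

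**The case against.** The case that this matters little is strong, and most of it stands.

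- **Hypothesis 1b is tested anyway.** The Aim 1 t test of the single-to-dual difference does not depend on the GEE. A reader might infer that the rule endangers hypothesis 1b, but it does not. That test is unadjusted, however, and belongs to the comparison within 48 h of injury, so it does not supply the later adjusted task-specific estimates.
- **Equality is not claimed.** A reader might infer that a non-significant interaction will be taken as proof of equal deficits. No section says so. The reduced model imposes a common difference, which is a modelling restriction and not a stated conclusion.
- **The Discussion sentence is a separate matter.** A reader might infer that impairment only under dual task will be declared when the dual-task test is significant and the single-task test is not. The plan states no such procedure, and the reduced GEE cannot produce that result. An equivalence margin is therefore not called for on this ground.
- **A high miss rate is not established.** For an excess of 0.5 outcome SD at one visit, the miss rate is 40% at r = 0.5, 19% at r = 0.7 and 6% at r = 0.8. If the plan's 0.72 applied to the dual-minus-single difference, it would be about 11%. Pooling over visits raises power for the two-way term.
- **An unseen analysis plan may say more about reporting.** That is possible, but the retention rule itself is fixed in the article.

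**Conclusion.** The point holds as a minor one. The rule selects the final Aim 2 model by the significance of terms that carry a named question, and it biases the adjusted task-specific differences toward each other when the deficits truly differ. Under the assumptions shown (one visit, outcome SD 1, deficits of 0.3 and 0.6 SD, r from 0.5 to 0.8), the bias is 0.04 to 0.08 SD, coverage is 89 to 93%, and kept interactions average 0.40 to 0.57 against 0.30. The article gives none of these assumed values. The single-visit figures ignore pooling in the GEE, which would reduce the distortion for an excess that is constant over visits. The primary Aim 1 and PostRTP t tests and the Aim 1 test of hypothesis 1b are unaffected.

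**What to change.** In the Aim 2 paragraph of the Phase 1 Statistical Analysis, replace the conditional clause. Both group × task and group × task × assessment should stay in the final GEE whatever their p-values. At each visit, report the mTBI-control difference under single task, under dual task, and their contrast, with 95% confidence intervals. Report the task-averaged difference from the same model as the overall result. Base any statement about dual-task-specific impairment on the group × task contrast and its interval. For the ordinal clinical score, apply the same rule on the model's own scale.

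The cost is a few extra model terms and wider intervals for the task-specific estimates: in the illustration, a standard error of 0.224 in place of 0.194 to 0.212. Every athlete performs both tasks, so with near-complete data the task-averaged difference loses essentially no precision. No further data are needed, but the change should be made before the analysis.
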